### Eligibility Criteria

Adults (aged over 18 years) admitted to general wards who are able to understand the participant information sheet are eligible for inclusion. Individuals with cardiac implantable electronic devices, who experience a skin reaction to the wearable sensor or its components, who have an open chest wound, or who withdraw consent will be excluded.

Recruitment will be aided by the responsible clinical team, who will deem individuals suitable to participate.

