### Outcome Measures

Outcome measures will include hospital length of stay; critical NEWS (defined as 7 or over); number of admissions to intensive care; mortality; sepsis events; and time to antibiotics.

To understand the acceptability and usability of the SensiumVitals system by participants and health care staff, mixed methods analysis (semistructured interviews and questionnaires) will be undertaken in the postimplementation phase. For participants, these interviews and questionnaires will be administered 24 hours after the SensiumVitals sensor has been applied, enabling familiarity with the sensor and maximizing of data capture before potential hospital discharge. Due to the nature of the shift patterns, a set time point has not been chosen for health care staff; however, the studies will only be conducted once familiarity with the system has been established. All key stakeholders will also be invited to take part in semistructured interviews to determine barriers and facilitators to implementing wearable sensors and alerting mechanisms within the hospital.

The questionnaires consist of 5-point Likert scale responses (strongly disagree to strongly agree), with elements adapted from the validated System Usability Scale [20].

Face-to-face interviews will be conducted by the lead researcher (FI) using a predetermined topic guide. Data collection will be an iterative process; emerging recurring concepts were incorporated into the interview guide for further exploration with remaining participants. Interviews will be recorded, anonymized, transcribed, and entered into NVivo 12 (QSR International) for analysis.

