### Statistical Analysis

The Shapiro-Wilk test will be used to check variables for Gaussian distribution. Data sets will be presented as absolute numbers of patients with the respective percentage per group or as parameter mean and standard deviation or median and range, depending on distribution. Descriptive statistics will describe the baseline characteristics of the participants, alerting frequencies, and events.

For comparisons of interval-scaled variables between the two groups, 2-tailed, unpaired *t* tests will be performed. Nonparametric between-group testing will be undertaken with 2-tailed Mann-Whitney U tests. Additionally, the chi-square test or Fisher exact test will be applied to nominal scale data.

Propensity score matching will be performed for differences among baseline demographics between pre-post phases, reducing bias from confounding variables. Analyses will be performed in SPSS (IBM Corporation), Stata (StataCorp LLC), and GraphPad (GraphPad Software Inc).

Mixed methods analysis will be undertaken for the questionnaire and semistructured interview data. Frequency distributions will be generated for Likert scale responses. Interview transcripts will be analyzed using thematic analysis [21]. The results will be discussed until consensus is reached.

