### Power Calculations

Formal power calculations are not possible on any of the outcomes, given the lack of surrounding data. However, Downey et al [22] estimated sample sizes of 325-625 for time to antibiotics after the first evidence of sepsis using the SensiumVitals sensor. A total of 226 participants were randomized; 140 had the sensor applied, and the remaining participants underwent usual care. All outcome measurements in this study demonstrated nonsignificant results. Therefore, we aim to recruit a minimum of 600 individuals, with approximately half in the preimplementation phase and the remaining participants in the postimplementation phase.

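### Time to antibiotics is left to a t or Mann-Whitney test, which cannot use septic participants who are never treated unless a rule is added; no time-to-event method is named

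*Protocol article*

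**What the plan says.** In the protocol article, Outcome Measures closes its list with "sepsis events; and time to antibiotics". That entry states no time origin, no population at risk and no rule for participants who are never treated.

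Statistical Analysis assigns tests by type of variable:

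- "The Shapiro-Wilk test will be used to check variables for Gaussian distribution".
- "For comparisons of interval-scaled variables between the two groups, 2-tailed, unpaired" *t* tests are to be used.
- "Nonparametric between-group testing will be undertaken with 2-tailed Mann-Whitney U tests".
- For categories, "the chi-square test or Fisher exact test will be applied to nominal scale data".

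Propensity score matching on baseline demographics is added. No survival, censoring or competing-risk method appears.

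Power Calculations mentions a time origin only when describing an earlier study, which "estimated sample sizes of 325-625 for time to antibiotics after the first evidence of sepsis". It then sets this trial's target: "we aim to recruit a minimum of 600 individuals, with approximately half in the preimplementation phase".

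Eligibility Criteria does not exclude people already receiving antibiotics: "Adults (aged over 18 years) admitted to general wards who are able to understand the participant information sheet are eligible for inclusion".

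**The concern.** Time to antibiotics is an event time, and the event may never happen. Under the stated scheme it is a numeric variable and goes to a *t* or Mann-Whitney test. Two groups of septic participants then cause difficulty.

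- **Never treated.** Someone who dies or leaves hospital before a first antibiotic has no time to enter, although this is the worst result the outcome can record. Left out, that result disappears from the comparison.
- **Already on antibiotics.** Someone on treatment when sepsis first shows has no forward delay. A zero or negative time would reflect earlier care, not the response to the sepsis.

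The two phases run one after the other, and the Discussion accepts that changes in care over time may bias the comparison. Either share could therefore differ by phase, and alerts could themselves change who is treated. Matching on baseline demographics does not supply the missing values. Time to antibiotics is also the only outcome for which the article cites a sample-size estimate.

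**Working it through.** **Figures in the article.** The target of 600 and the cited range of 325-625 cannot be reproduced, because no alpha, power, effect size, SD or sepsis rate is given. This point disputes neither figure.

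**What follows from the text.** Time to antibiotics is numeric, and the named numeric tests are *t* and Mann-Whitney. Each takes one value per person, and a never-treated participant has none. Some further rule is needed before that person can enter either test, and the article gives none.

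**Assumed inputs for size.** The documents give no delay distribution and no shares, so everything below is illustrative. Delay is lognormal with log SD 1. A quantile *q* then equals median × exp(z_q).

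*1. Slowest cases untreated, completed times only (median 3 h in both phases).* If the slowest fraction *f* is never treated, the completed-case median is the (1 − f)/2 quantile of the full distribution.

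| f | Quantile | z | Factor | Median (h) |
|---|---|---|---|---|
| 5% | 0.475 | −0.063 | 0.939 | 2.82 |
| 15% | 0.425 | −0.189 | 0.828 | 2.48 |
| 20% | 0.400 | −0.253 | 0.776 | 2.33 |

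For 15% v 5% the gap is about 0.33 h (unrounded values); for 20% v 5% it is 0.49 h. The phase that leaves more people untreated looks faster. If the untreated were kept and ranked after every observed time, the median would be 3 h in both phases.

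*2. Already-treated entered as zero (30% in both phases, true medians 3 h and 2 h).* The overall median is the (0.5 − 0.3)/0.7 = 0.286 quantile of the positive times; z = −0.566, factor 0.568.

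- 3 × 0.568 = 1.70 h and 2 × 0.568 = 1.14 h.
- The 1.00 h difference becomes 0.57 h, a 43% loss in absolute hours.
- The ratio is unchanged: 1.14/1.70 = 0.67 = 2/3.

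*3. Effect on the Mann-Whitney test.* Simulation with 60 septic participants per phase (20% of an assumed 300), 3,000 runs, two-sided 0.05. The table gives rejection rates. Never treated is 10% in both phases unless stated, and here non-treatment is unrelated to speed.

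| Scenario (pre v post) | Both groups dropped | Never-treated dropped, already-treated as 0 | Already-treated excluded, never-treated worst rank |
|---|---|---|---|
| 4 v 4 h; already treated 20% v 20% | 0.05 | 0.05 | 0.05 |
| 4 v 4 h; already treated 20% v 35% | 0.05 | 0.33 | 0.06 |
| 4 v 4 h; already treated 20% v 20%; never treated 25% v 10% | 0.05 | 0.07 | 0.36 |
| 4 v 2.8 h; already treated 20% v 20% | 0.34 | 0.19 | 0.25 |
| 4 v 2.8 h; already treated 35% v 20% | 0.31 | 0.11 | 0.29 |

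In the last row the zero-coded medians reverse, to 1.6 v 2.0 h, although the post phase is truly faster.

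**The case against.** The strongest reply is that this is a condensed article. It names tests by variable type and never explicitly assigns one to this outcome. Risk sets and censoring rules usually sit in the full protocol or SAP, neither of which is shown. That protects the article from a charge of omission. It does not remove the mismatch, because the article does state its between-group methods and none is built for an event that may not occur.

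A reader might infer several stronger things that the documents do not support:

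- **That untreated cases will be dropped or already-treated cases scored as zero.** Nothing in the article says so. The consequences above are conditional on those choices.
- **That neither test can be made to work.** Neither test requires non-negative values, and Mann-Whitney can hold never-treated participants at the worst rank.
- **That the already-treated group forces a change of test.** It does not. Defining the at-risk set deals with this group under any test.
- **That the 0.33 h gap arises with no true difference.** A phase with 15% untreated does differ from one with 5%. The example shows completed times pointing the wrong way about that difference, and it assumes that the untreated are the slowest. Where non-treatment is unrelated to speed, dropping does not bias the timing contrast; it hides the difference in treatment (0.05 v 0.36 above).
- **That 43% of the effect is lost on any scale.** The ratio of medians is untouched, and Mann-Whitney is not a test of medians.

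Two further replies stand. With equal shares and no effect, every handling keeps type I error near 0.05. With equal shares and a real timing effect, the worst-rank test had less power than dropping (0.25 v 0.34). Time to antibiotics is also one of six listed outcomes, with none named as primary.

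**Conclusion.** The point holds as a mismatch between outcome and method. Under the stated tests, time to antibiotics cannot use never-treated septic participants without an added rule, and no time-to-event method is named. The harm is conditional. Analysing completed times only hides a phase difference in the share never treated, or biases the contrast if the untreated are the slow cases. Entering already-treated participants as zero dilutes the absolute difference, and unequal shares can then produce a false effect.

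The size is unknown, because the documents give no proportions. The gap of about 0.33 h rests on a lognormal delay with median 3 h and log SD 1, and on the slowest 15% v 5% being untreated. The 0.33 rejection rate rests on 60 septic participants per phase and on already-treated shares of 20% v 35%. The documents do not support saying that the comparison is distorted, only that the stated method leaves it open to distortion. It should be corrected before analysis.

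**What to change.** Amend Statistical Analysis for this outcome as follows.

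1. State time zero, and define the at-risk set as septic participants not on antibiotics at that time.
2. Analyse time to first antibiotic by cumulative incidence in each phase, with death and discharge before antibiotics as competing events, so that untreated participants stay in the denominator. A simpler acceptable alternative is a Mann-Whitney test with never-treated participants at the worst rank.
3. Report the between-phase contrast with a 95% CI.
4. Tabulate by phase the number already on antibiotics at time zero and the number never treated.

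The cost is mainly wording. The case notes and electronic health records named under Data Collection should hold the antibiotic, death and discharge times. The downside is a slightly smaller analysed group and a summary less familiar than a median. The worst-rank alternative can also lose some power when the never-treated shares are equal, as shown above.

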### Statistical Analysis

The Shapiro-Wilk test will be used to check variables for Gaussian distribution. Data sets will be presented as absolute numbers of patients with the respective percentage per group or as parameter mean and standard deviation or median and range, depending on distribution. Descriptive statistics will describe the baseline characteristics of the participants, alerting frequencies, and events.

For comparisons of interval-scaled variables between the two groups, 2-tailed, unpaired *t* tests will be performed. Nonparametric between-group testing will be undertaken with 2-tailed Mann-Whitney U tests. Additionally, the chi-square test or Fisher exact test will be applied to nominal scale data.

Propensity score matching will be performed for differences among baseline demographics between pre-post phases, reducing bias from confounding variables. Analyses will be performed in SPSS (IBM Corporation), Stata (StataCorp LLC), and GraphPad (GraphPad Software Inc).

Mixed methods analysis will be undertaken for the questionnaire and semistructured interview data. Frequency distributions will be generated for Likert scale responses. Interview transcripts will be analyzed using thematic analysis [21]. The results will be discussed until consensus is reached.

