## Methods

### Study Design

This is a single-center, pre-post design in which digital alerting systems are implemented on acute wards. The preimplementation phase dated from September 2017 to August 2019, and the postimplementation phase is currently underway.

The preimplementation phase involved using the SensiumVitals system in accordance with usual care. However, health care staff were not able to view the continuous vital sign monitoring data or the digital alerts generated for abnormal parameters. Usual care, in our institution, involves intermittent monitoring of vital signs in accordance with NEWS2.

In the postimplementation phase, alerting systems following recognition of abnormal parameters will be included. These alerts will be transmitted to mobile devices and central monitoring hubs, with alert acknowledgement required from health care staff.

All participants provided informed consent. Ethical approval for this study has been granted by a Research Ethics Committee (Integrated Research Application System: 222979). The trial will be performed in accordance with Good Clinical Practice guidelines and the Declaration of Helsinki. Patient data will be anonymized to ensure privacy. Storage and handling of personal data will comply with the General Data Protection Regulation.

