### Intervention Protocol for Alerts

All alerts will be viewed by dedicated trained nursing staff covering the wards. Alerts will be generated when measured vital signs exceed pre-established thresholds for 10 consecutive minutes. These thresholds can be individually tailored but are initially programmed to trigger if the patient’s temperature exceeds 38.1 ºC, respiratory rate is over 25 breaths per minute, and heart rate is over 131 beats per minute, in accordance with NEWS2 cutoffs [14]. All incoming alerts are deemed to be of potential clinical relevance, and potential outcomes include but are not limited to reviewing the individual, repeating observations, increased frequency of monitoring, and escalation to a responsible physician.

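### Alerting works at ward level, but the between-phase tests and the stated matching leave ward out, so a change in ward mix or ward-specific drift could pass for an alert effect

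*Protocol article*

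**What the plan says.** Study Design sets the level and timing of the intervention: "This is a single-center, pre-post design in which digital alerting systems are implemented on acute wards". There is one changeover: "The preimplementation phase dated from September 2017 to August 2019, and the postimplementation phase is currently underway". Intervention Protocol for Alerts says who responds: "All alerts will be viewed by dedicated trained nursing staff covering the wards". The Discussion adds that the radio bridges carrying the data are installed on wards.

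Statistical Analysis names the comparisons between phases. Besides the unpaired t test ("For comparisons of interval-scaled variables between the two groups, 2-tailed, unpaired *t* tests will be performed") there are two others: "Nonparametric between-group testing will be undertaken with 2-tailed Mann-Whitney U tests" and "Additionally, the chi-square test or Fisher exact test will be applied to nominal scale data". The one adjustment is this: "Propensity score matching will be performed for differences among baseline demographics between pre-post phases, reducing bias from confounding variables".

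Power Calculations sets the size: "we aim to recruit a minimum of 600 individuals, with approximately half in the preimplementation phase and the remaining participants in the postimplementation phase". Eligibility Criteria leaves it to the responsible clinical team to judge who is suitable. No section gives the number of wards, or says whether the same wards recruit in the same proportions in both phases.

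**The concern.** Patients on one ward share staff, specialty, discharge practice and response to alerts, so outcomes such as length of stay are likely to be correlated within a ward. All four named tests treat patients as independent, and ward is not among the stated matching variables. Two things can then go wrong.

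- **Ward mix.** If wards contribute different shares of patients before and after, standing differences between wards enter the phase contrast.
- **Ward-by-phase drift.** If a ward changes for its own reasons (a new team, a local pathway), that change averages out over the number of wards. The tests behave as if it averaged out over about 300 patients.

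In either case the p-value and interval are too optimistic, and a difference that has nothing to do with alerts may be reported as significant. This matters because the Discussion hopes the results will show effectiveness.

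**Working it through.** **The plan's own figure.** The total of 600 cannot be reproduced, because no alpha, power, effect size, SD or event rate is given. For scale only, 300 per phase with an assumed two-sided 5% level and 80% power detects (1.960 + 0.842) × √(2/300) = 0.229 SD.

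**Inputs.** From the document: about 300 per phase, two-sided tests, patient as the unit. Assumed: the 5% level, number of wards k, ICC, correlation of a ward's effect between phases (c), and ward shares. The outcome is continuous with total variance 1, and there is no alert effect.

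**Formulas.** With p and q the ward shares in the two phases:

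- Equal shares, true variance of the difference = 2[(1 − ICC)/300 + ICC(1 − c)/k].
- Shifted shares with stable ward effects (c = 1), true variance = 2(1 − ICC)/300 + ICC × Σ(p − q)².
- Variance used by the t test ≈ 2[1 − ICC + ICC(1 − Σp²)]/300.
- Actual rejection rate = 2[1 − Φ(1.96/√ratio)], where ratio = true variance / variance used.

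**Same mix, stable effects (c = 1).** Ward is crossed with phase and cancels. The formula gives 4.5-4.9% for 2 to 10 wards and ICC 0.01-0.05, so there is no inflation.

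**Mix shift, 4 wards, ICC 0.05, c = 1.**

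- *40 points.* Shares 0.4, 0.3, 0.2, 0.1, reversed in the second phase, give Σ(p − q)² = 0.09 + 0.01 + 0.01 + 0.09 = 0.20. True variance = 0.00633 + 0.0100 = 0.01633; used = 0.00657; ratio 2.49; rejection 21% (20% in simulation).
- *20 points.* Half that shift gives Σ(p − q)² = 0.05. True variance = 0.00633 + 0.0025 = 0.00883; used = 0.00658; ratio 1.34; rejection 9.1%.
- *10 points.* Rejection 5.7%.

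With 10 wards and ICC 0.05, shifts of 33, 17 and 8 points give 9.7%, 5.8% and 4.8%. With 4 wards and ICC 0.02, the 20-point shift gives 6.6% and the 40-point shift 12.0%.

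**Ward-by-phase drift, equal mix.** For 4 wards, ICC 0.05 and c = 0.8, true variance = 2(0.95/300 + 0.01/4) = 0.0113, against 2/300 = 0.0067. The ratio is 1.70 and rejection about 13% (two simulations gave 13.7% and 14.7%). Over other assumptions:

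| Wards | ICC | c = 0.8 | c = 0.5 |
|---|---|---|---|
| 4 | 0.01 | 6.7% | 9.4% |
| 4 | 0.02 | 8.4% | 13.7% |
| 4 | 0.05 | 13.5% | 24.7% |
| 10 | 0.01 | 5.6% | 6.7% |
| 10 | 0.02 | 6.2% | 8.4% |
| 10 | 0.05 | 8.0% | 13.4% |

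**What ward adjustment recovers** (simulation, 4 wards, ICC 0.05):

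| Scenario | Plain t test | Ward fixed effects | Paired ward-phase means |
|---|---|---|---|
| 40-point shift, c = 1 | 20.1% | 3.9% | 3.9% |
| Equal mix, c = 0.8 | 14.7% | 15.4% | 5.7% |
| Both | 26.4% | 12.8% | 4.7% |

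Ward as a factor deals with the mix shift and does nothing for drift. The paired comparison holds its level, but has only 3 degrees of freedom with 4 wards.

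**The case against.** Much of the opposing case limits the point, and some of it stands.

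- **Staggered activation.** A reader might infer that alerts are switched on one ward at a time. The article describes a single changeover, and its wording on nursing cover fits a pool shared across wards as well as ward-specific responders. The point needs only a ward-level intervention.
- **Clustering as such.** A reader might infer that any difference between wards inflates error. It does not: stable ward effects cancel when the same wards recruit in the same mix.
- **An actual shift in mix.** Clinical teams judging suitability does not show that ward shares changed, and no section says they did. A 40-point shift is extreme. At about 10 points the error rate is close to nominal.
- **Matching and unseen documents.** A fuller plan may well list more matching variables than a condensed article, and including ward could remove a mix shift. But the article states both the scope of the matching and the tests, and neither mentions ward. Matching on ward would not remove drift.
- **Limitation already conceded.** The Discussion says cause and effect cannot be established and that changes over time may bias the comparison. That is fair on interpretation, but it does not correct an interval that is too narrow.
- **Outcome type.** The calculations use a continuous outcome. The mechanism carries over to binary outcomes, but these error rates need not.

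**Conclusion.** The point holds conditionally. The intervention acts on wards, and the stated analysis ignores ward, so a changed ward mix or ward-specific drift can be read as an alert effect. Whether either occurred cannot be known from the article.

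Under the assumptions above (300 per phase, 4 wards, ICC 0.05), a nominal 5% t test rejects about 9% for a 20-point mix shift, about 20% for a 40-point shift, and about 13% with equal mix and c = 0.8. With 10 wards, or ICC 0.01-0.02, inflation is smaller and often leaves 5-8%, although strong drift or an extreme shift still takes it higher. With the same mix and stable ward effects there is none.

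The article therefore does not support saying that the planned p-values are wrong. It supports saying that they are unprotected against two plausible disturbances, one of which can be removed at little cost.

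**What to change.** Amend Statistical Analysis as follows.

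1. Record ward at sensor application and report recruitment by ward and phase, so that any mix shift is visible.
2. Include ward in the matching, exactly where numbers allow.
3. Compare phases with ward-stratified methods: regression with ward as a factor for length of stay and time to antibiotics, and Cochran-Mantel-Haenszel or logistic regression with ward for binary outcomes. Base the effectiveness statement on these estimates.
4. State that steps 2 and 3 remove the ward-mix part only. As a sensitivity analysis for drift, report a paired comparison of ward-phase means, or a ward-by-phase random intercept with a small-sample correction, and say that it is imprecise with few wards.

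None of this removes a hospital-wide time trend, so the caveat in the Discussion should stay.

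The cost is a change of wording and no extra patients. Ward should be available from the admissions system that Stakeholder Engagement says is integrated with the monitoring software, or from the records already under review. The downsides are some unmatched patients, especially if a ward recruited in one phase only, sparse strata for rare outcomes and for time to antibiotics, and wide intervals in step 4.

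### The only stated confounding control is propensity matching on baseline demographics, so a between-phase difference in illness severity or case mix would stay in the comparison

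*Protocol article*

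**What the plan says.** The protocol article describes a single-centre pre-post study (Study Design). The first phase ran from September 2017 to August 2019 and the second followed. On who enters, Eligibility Criteria says: "Recruitment will be aided by the responsible clinical team, who will deem individuals suitable to participate".

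Statistical Analysis names these between-phase tests:

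- Student's t, introduced with the words "For comparisons of interval-scaled variables between the two groups, 2-tailed, unpaired";
- a rank test as the alternative: "Nonparametric between-group testing will be undertaken with 2-tailed Mann-Whitney U tests";
- and, for categorical outcomes such as death: "Additionally, the chi-square test or Fisher exact test will be applied to nominal scale data".

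The one adjustment step is: "Propensity score matching will be performed for differences among baseline demographics between pre-post phases, reducing bias from confounding variables". No severity, comorbidity, admission-type or ward variable is named. Two paragraphs earlier, the same section uses the wider term baseline characteristics for what will be described.

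On size, Power Calculations says: "we aim to recruit a minimum of 600 individuals, with approximately half in the preimplementation phase". It gives no effect size, SD or event rate: "Formal power calculations are not possible on any of the outcomes, given the lack of surrounding data".

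**The concern.** All six clinical outcomes plausibly depend on how ill the patient is on entry. Age and sex carry only part of that. If the second phase enrols sicker or healthier patients, or a different mix of wards and emergency admissions, matching on demographics leaves most of the shift in place and a covariate-free test attributes it to the alerts. The bias could run in either direction.

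There are two routes to such a shift. Time separates the phases, so case mix can drift. Phase is also not concealed from staff: they could not see the data or alerts in the first phase and must acknowledge alerts in the second, and the clinical team judges who is suitable.

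The matching sentence claims to reduce confounding in general, which is more than demographic variables can deliver. Its reference to differences between phases can also be read as choosing variables by observed imbalance instead of prognostic importance.

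**Working it through.** **1. The plan's own figure.** The 600 cannot be reproduced. The article gives no alpha, power, effect size, SD or event rate. It cites another study that "estimated sample sizes of 325-625 for time to antibiotics after the first evidence of sepsis using the SensiumVitals sensor", and 600 lies inside that range. Everything below is therefore illustrative, using 300 per phase from the article and assumed values elsewhere (two-sided 5% level).

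**2. Simple bound.** If a severity variable is left unadjusted, bias (in outcome SD) = imbalance s × severity-outcome correlation r. The standard error is √(2/300) = 0.0816.

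| s (SD) | r | Bias = s × r | Bias / SE | False-positive rate |
|---|---|---|---|---|
| 0.1 | 0.3 | 0.03 | 0.37 | 6.6% |
| 0.3 | 0.3 | 0.09 | 1.10 | 19.7% |
| 0.3 | 0.5 | 0.15 | 1.84 | 45.1% |
| 0.5 | 0.5 | 0.25 | 3.06 | 86.5% |

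Rate = 1 − Φ(1.96 − bias/SE) + Φ(−1.96 − bias/SE). This gives demographics no credit for carrying severity.

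**3. Null simulation with matching.** Assumptions: no alert effect; 300 per phase; 600 replicates; age shifted 0.2 SD; age-severity correlation 0.2; outcome = 0.2 × age + 0.4 × severity + noise with variance 0.75. Matching was 1:1 with a caliper of 0.2 SD of the logit, analysed by unpaired t test. The ratio and caliper are choices made for this check and are not in the article.

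| Severity shift | Demographic-only matching: bias; false positives | Severity added to the propensity score: bias; false positives | Regression on all 600: bias; false positives |
|---|---|---|---|
| 0 | −0.021; 5.0% | −0.005; 3.5% | −0.005; 5.8% |
| 0.2 | 0.065; 10.3% | 0.001; 3.0% | 0.000; 4.5% |
| 0.3 | 0.108; 24.0% | 0.006; 2.0% | 0.005; 4.0% |
| 0.5 | 0.187; 61.3% | 0.003; 2.2% | 0.000; 5.2% |

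**4. Check of the simulation by hand.** Matching on age removes the part of the severity shift that age predicts, 0.2 × 0.2 = 0.04. Expected residual bias = 0.4 × (s − 0.04), which is 0.064, 0.104 and 0.184 for s = 0.2, 0.3 and 0.5. The simulation gave 0.065, 0.108 and 0.187. Outcome variance is 0.04 + 0.16 + 2 × 0.2 × 0.4 × 0.2 + 0.75 = 0.982 (SD 0.991). With 266 pairs the SE is 0.991 × √(2/266) = 0.086. For s = 0.3, 0.108/0.086 = 1.26, giving a rate of 24%, as simulated.

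**5. A binary outcome, for scale.** Assume risks of 5% (low severity) and 15% (high severity), with the high-severity share rising from 20% to 30%. Phase risks are 0.8 × 5% + 0.2 × 15% = 7.0% and 0.7 × 5% + 0.3 × 15% = 8.0%, a risk ratio of 1.14 with no alert effect. At 300 per phase that is 21 v 24 events. The pooled risk is 0.075, the SE is √(0.075 × 0.925 × 2/300) = 0.0215, and z = 0.01/0.0215 = 0.465 (p = 0.64). The estimate is distorted, but a shift of this size would seldom produce a significant result by itself.

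**The case against.** The strongest case against is that this is a condensed article. Propensity covariates are ordinary analysis-plan detail, and the phrase baseline demographics may be loose wording for baseline characteristics. That is possible. But the sentence does more than omit a list: it states what the matching is for, in a narrower term than the section uses for description. If more was meant, the sentence misstates the plan and should be corrected anyway.

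Second, differential recruitment is a hypothesis. The article gives one set of eligibility criteria for both phases and does not say that judgements of suitability change. This stands: the risk is plausible but not shown.

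Third, the Discussion says that the design cannot establish cause and effect and names longitudinal change as a source of bias. That disclosure deserves credit. It does not mention case mix or selection, and it does not replace adjustment for severity data that are available.

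A reader might infer three stronger points that the article does not support:

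- *That matching will discard a known share of patients and so cost power.* Matching drops unmatched patients, but the article gives no ratio, caliper or rule for them, and 600 is a minimum.
- *That unpaired tests after matching leave confounding in.* The article does not say that the tests are run on the matched set. Ignoring pairing is in any case conservative: the true level is 2 × (1 − Φ(1.96/√(1 − ρ))), or 3.9%, 2.8% and 1.9% for within-pair correlations of 0.1, 0.2 and 0.3.
- *That matching is the wrong method.* Once severity is in the propensity score, bias in the simulation is 0.006 SD or less.

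**Conclusion.** The concern holds in a limited form. As worded, confounding control extends only to demographics, every named between-phase test is covariate-free, and the outcomes depend on acuity. Any severity or case-mix difference that demographics do not carry would stay in the between-phase comparison, and the claim to reduce confounding is wider than the named variables support.

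The size cannot be fixed from the article. Under the simulation's assumptions, false-positive rates ran from about 10% to 61% for severity imbalances of 0.2 to 0.5 SD, against 2% to 5% with severity included. They stayed at 5% when severity was balanced. Monte Carlo error is about 1 to 2 percentage points on the inflated rates. The binary example shows that a modest shift can be too small to matter for significance.

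This should be corrected before analysis, but the evidence does not show that the trial's result will be biased. Confidence is moderate, because an unseen plan may already name the covariates.

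**What to change.** In Statistical Analysis, replace baseline demographics with a list of prognostic covariates fixed in advance and used whether or not they differ between phases: age, sex, comorbidity, emergency or elective admission, ward or specialty, and the last routine NEWS before the sensor was applied. State that the analysis adjusted for these is the main between-phase comparison and that the unadjusted tests are supportive.

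Matching, weighting or outcome regression with this set is acceptable. If matching is kept, report how many patients go unmatched and are dropped.

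The cost is small. Study Design says that intermittent NEWS2 monitoring is usual care, and Data Collection already lists case notes and electronic health records as sources. Expect some extra extraction and some missing covariate values, so a rule for those is needed. The change does not remove secular change, and the Discussion's caution on that should stay.
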